## Abstract

**Background:** Type 2 diabetes mellitus (T2DM) complicated with dyslipidaemia is associated with a high risk of cardiovascular diseases. The Jiangtang Tiaozhi (JTTZ) recipe is a Chinese herbal formula that has been used to regulate the blood glucose and lipid levels for many years. Interestingly, a previous study has demonstrated its efficacy; however, the associated mechanism remains unclear. We hypothesised that the therapeutic effect of the JTTZ on patients with T2DM may be mediated by the modulation of metabolites secreted by the gut microbiota. This study aims to examine this mechanism.

**Methods and analysis:** This study is a randomised, positive drug parallel-controlled, open-label clinical trial in patients with T2DM and dyslipidaemia. A total of 96 patients will be recruited and randomly assigned to treatment with JTTZ or metformin for 12 weeks. The primary outcome will be the rates of effectively regulated blood glucose and lipid levels (measured with the levels of glycated haemoglobin, fasting plasma glucose, 2-h plasma glucose, triglyceride, and low-density lipoprotein cholesterol). The secondary outcomes will be the changes in body weight, body mass index, and waist circumference and Traditional Chinese Medicine symptom scores. In addition, 16S rRNA gene sequencing will be performed on the gut microbiota obtained from faeces, and metabolomics analysis will be performed based on blood and gut microbiota samples. Intention-to-treat, per-protocol analysis and safety analysis will be performed.

**Clinical trial registration number: **
https://clinicaltrials.gov/ct2/show/NCT04623567

## Background

Type 2 diabetes mellitus (T2DM) and dyslipidaemia are associated with an increased cardiovascular disease (CVD) risk. (Wilson et al., 1998) (Gerstein et al., 2005). Although dyslipidaemia is an independent risk factor for CVD, it plays a major role in the context of T2DM-induced CVD. (Eliasson et al., 2011) (Turner et al., 1998). The prevalence of T2DM and dyslipidaemia are estimated to be 11.2% (Li et al., 2020) and 34% (Pan et al., 2016) in China, respectively. Meanwhile, the prevalence of dyslipidaemia in patients with T2DM is estimated at 67.1%, (Yan et al., 2016), suggesting a need for a comprehensive approach to the treatment of patients with T2DM and dyslipidaemia. Statin use is the first-line approach to low-density lipoprotein cholesterol (LDL-C) level lowering and cardioprotection prescribed in addition to lifestyle interventions and glycaemic control in patients with T2DM complicated with dyslipidaemia. However, the use of a single stain may not achieve the recommended control levels or may be poorly tolerated. Meanwhile, combination treatments are not recommended because of the lack of evidence for their efficacy. (American Diabetes Association, 2020) (Jia et al., 2019). Metformin is the first-line pharmacologic treatment for T2DM (American Diabetes Association, 2019); a growing body of evidence supports its performance in antiatherosclerosis and CVD risk reduction among T2DM patients. (Petrie et al., 2020). In addition, metformin may activate adenosine 5‘-monophosphate -activated protein kinase and reduce the LDL-C levels. (Xu et al., 2015a).

Traditional Chinese Medicine (TCM) approaches reportedly improve glycaemic control, blood lipid levels, and weight management. (Wu et al., 2020). In fact, a TCM herbal formula may ameliorate blood glucose and lipid levels by shifting the composition of the gut microbiota. (Tong et al., 2018). The Jiangtang Tiaozhi (JTTZ) recipe has been used to treat patients with T2DM with dyslipidaemia for many years. (Zhao, 2013). Interestingly, the findings from a multi-centre trial suggested that it is safe and effective in the management of the blood glucose levels, lipid levels, and weight in patients with T2DM with obesity and hyperlipidaemia. (Yu et al., 2018). The formula consists of eight Chinese herbs, including Aloe [*Aloe vera* (L.) Burm. f. or *Aloe ferox* Mill. (Asphodelaceae)], *Coptidis rhizoma* [*Coptis chinensis* Franch., *Coptis teeta* Wall., or *Coptis deltoidea* C.Y.Cheng and P.K.Hsiao (Ranunculaceae)], *Anemarrhenae rhizoma* [*Anemarrhena asphodeloides* Bunge (Asparagaceae)], red yeast rice [*Fermentum Rubrum* (Aspergillaceae)], bitter melon [*Momordica charantia* L. (Cucurbitaceae)], *Salvia miltiorrhizae radix et rhizoma* [*Salvia miltiorrhiza* Bunge (Lamiaceae) ], *Schisandrae chinensis fructus* [*Schisandra chinensis* (Turcz.) Baill. (Schisandraceae)], and *Zingiberis rhizoma* [*Zingiber officinale* Roscoe (Zingiberaceae)]. In the TCM theory, the JTTZ recipe clears the excess heat in the stomach and intestines, thus alleviating patients’ symptoms. However, the mechanism underlying the clinical efficacy of the JTTZ recipe remains unknown. We hypothesised that the JTTZ may exert a therapeutic effect equal to or better than that exerted by metformin among patients with T2DM with dyslipidaemia, and that this effect may be mediated by the modulation of metabolites secreted by the gut microbiota. Therefore, a randomised, positive drug parallel-controlled, open-label clinical trial was designed; 16S rRNA gene sequencing as well as gas chromatography/time-of-flight mass spectrometry analyses will be performed to explore these mechanisms.

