## Methods

### Study Design

This study is a randomised, positive drug parallel-controlled, open-label, non-inferiority clinical trial in patients with glucose and lipid metabolism disturbances. In total, 96 patients diagnosed with T2DM and dyslipidaemia will be recruited for this study. The patients will be randomly divided into two groups and treated with the JTTZ recipe or metformin for 12 weeks. This study protocol follows the Standard Protocol Items: Recommendations for Interventional Trials. (Chan et al., 2013). (Supplementary File S1). The study flow is illustrated in Figure 1. All information related to the treatment schedule is presented in Table 1.

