### Primary Outcomes

The changes of HbA1c levels are the primary study outcomes Besides, the rates of effectively regulated HbA1c, FPG, 2 h-PG, TG, and LDL-C levels will be calculated based on the number of patients who make the target achievement. The HbA1c level ≤7%, FPG level ≤7.0 mmol/L (126 mg/dl), 2 hP G level ≤10.0 mmol/L (180 mg/dl), TG level ≤1.7 mmol/L (150 mg/dl), LDL-C level ≤3.3 mmol/L (130 mg/dl) will be set as the target achievement. The FPG levels will be tested during the screening period, before intervention, and every 4 weeks during the treatment period. The levels of HbA1c, 2 h-PG, TG, and LDL-C will be recorded during the screening period, at the beginning and at the end of the12-week treatment period.

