## Discussion

This trial is designed as a randomised, positive drug parallel-controlled, open-label clinical trial. This trial will provide evidence on the effectiveness of the JTTZ recipe in regulating the blood glucose and lipid levels in patients with T2DM and dyslipidaemia. In addition, metabolomic analysis of the intestinal microorganisms may partially reveal the mechanism of the JTTZ recipe action on the intestinal microorganisms, blood glucose, and lipid metabolism.

Several studies have shown the importance of the gut microbiota in the pathophysiology of T2DM, and bacterial taxa, including the genera *Bifidobacterium, Bacteroides, Fusobacterium*, and *Blautia.* The treatment for T2DM may modulate inflammation and gut permeability, among others. (Gurung et al., 2020). A previous study showed that the intestinal flora was associated with the risk of developing T2DM, and the changes in the intestinal flora metabolites, such as short-chain fatty acid butyrate, may improve insulin response. (Sanna et al., 2019). In addition, some bacteria may contribute to the host glucose and lipid homeostasis. (Kuno et al., 2018). Our previous study demonstrated that T2DM may be alleviated by structural modulation of the gut microbiota using a traditional Chinese herbal formula, the Gegen Qinlian Decoction. (Xu et al., 2015b). The present study aims to validate the involvement of the gut microbiota in T2DM complicated with dyslipidaemia management and to identify the relevant genera of intestinal microorganisms.

This study has some limitations. First, the outcomes may be influenced by the open-label nature of this study. In addition, this is a single-centre study in China. Thus, the generalisability of any findings remains unclear.

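### The non-inferiority hypothesis is not limited to glucose, and a lipid result merely similar to metformin's would not show that JTTZ regulates lipids

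*Protocol article*

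**What the plan says.** The Background gives the only efficacy hypothesis: "the JTTZ may exert a therapeutic effect equal to or better than that exerted by metformin", in patients with T2DM and dyslipidaemia. Study Design calls the study a "randomised, positive drug parallel-controlled, open-label, non-inferiority clinical trial in patients with glucose and lipid metabolism disturbances". Neither place names the endpoint to which non-inferiority applies.

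Lipids stand among the primary outcomes in both descriptions. The Abstract says "The primary outcome will be the rates of effectively regulated blood glucose and lipid levels" and lists TG and LDL-C. The Primary Outcomes section puts change in HbA1c first, then adds that "the rates of effectively regulated HbA1c, FPG, 2 h-PG, TG, and LDL-C levels will be calculated", with "TG level ≤1.7 mmol/L (150 mg/dl), LDL-C level ≤3.3 mmol/L (130 mg/dl) will be set as the target achievement".

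The Discussion states the intended conclusion: "This trial will provide evidence on the effectiveness of the JTTZ recipe in regulating the blood glucose and lipid levels".

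On the comparator, the Background presents metformin as first-line drug treatment for T2DM and statins as first-line for lowering LDL-C. Its only statement on metformin and lipids is that the drug may activate a kinase and "reduce the LDL-C levels". No size is given, and TG is not mentioned. Sample Size gives an expected HbA1c reduction for metformin and no lipid figure. There are two arms, JTTZ and metformin, and earlier lipid-lowering agents are continued (Interventions).

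**The concern.** A result equal to an active control shows efficacy only if the control is known to work on that endpoint. The article supplies this for HbA1c. It does not for LDL-C or TG, although hypothesis, primary outcomes and announced conclusion all run glucose and lipids together. A product with no effect on lipids could give LDL-C and TG results close to metformin's. Under an equal-or-better hypothesis that is not limited to glucose, this could be reported as lipid regulation. What is at stake is the lipid half of the trial's conclusion, not the HbA1c comparison.

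**Working it through.** **1. The plan's own figure.** Sample Size gives HbA1c reductions of 1.0 and 0.9, z-values of 1.960 and 0.842, and sigma 0.024.

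- n per group = 2 × 0.024 × (1.960 + 0.842)² / 0.1² = 37.7, rounded up to 38.
- With 20% dropout: 38 / 0.80 = 47.5, rounded up to 48; total 96.

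The stated figures reproduce if 0.024 is read as a variance; as an SD the same formula gives 1 per group. For this point, what matters is that every input is an HbA1c input.

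**2. What the article supplies for each endpoint.**

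| | HbA1c | LDL-C | TG |
|---|---|---|---|
| Among the primary outcomes | yes | yes (target rate) | yes (target rate) |
| Metformin effect | first-line glucose drug, reduction of 1.0 | hedged, no size | nothing |
| Treatment named as first-line | metformin (for T2DM) | statin | none named |
| Sample-size input | yes | no | no |
| Written test of rates | two-sided chi-square or Fisher | same | same |

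**3. What similarity can show.** For any endpoint,

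(JTTZ − no treatment) = (JTTZ − metformin) + (metformin − no treatment).

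The trial estimates the first term on the right; the second must come from outside it. For HbA1c the article offers 1.0. For LDL-C it offers a direction without a size, and for TG nothing. If the first term is near zero, the lipid effect of JTTZ is therefore whatever metformin's is, which the article leaves unknown. If the first term favours JTTZ, an effect is shown, provided that metformin does not itself worsen lipids.

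**4. Illustration.** The article gives no lipid rates, so these are assumptions: JTTZ does nothing and 20% reach target; metformin brings 30% to target.

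With 48 per arm:

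- SE under equality = √(2 × 0.25 × 0.75 / 48) = 0.0884.
- SE under the true rates = √((0.2 × 0.8 + 0.3 × 0.7) / 48) = 0.0878.
- P(no significant difference) = Φ((1.96 × 0.0884 − 0.10) / 0.0878) − Φ((−1.96 × 0.0884 − 0.10) / 0.0878) = 0.80.

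With 38 per arm the same steps give 0.83. At assumed JTTZ rates of 10%, 30% and 50%, again with metformin 10 points higher and 48 per arm, the values are 0.72, 0.83 and 0.84.

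**5. Can the target rates within the JTTZ arm replace a control?** Entry requires LDL-C ≥3.4 and TG >1.7 mmol/L; the targets are ≤3.3 and ≤1.7. Some patients will cross by regression to the mean. The inputs are assumed: LDL-C SD 0.9, within-person SD 0.25–0.35, mean 3.2–4.0 mmol/L; log-normal TG with log SD 0.5, within-person log SD 0.18–0.25, median 1.7–2.2 mmol/L.

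- Each cut-off applied alone: 4–16% at the LDL-C target and 10–23% at the TG target with no drug effect.
- Both cut-offs plus LDL-C ≥4.1 or TG ≥2.3 mmol/L: about 3–13% and 6–18%. The other diagnostic routes are not modelled and would move these up.

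This affects both randomised arms alike and does not bias their comparison. It means only that a raw target rate within one arm is not evidence of a lipid effect.

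**The case against.** The strongest reply is that no lipid non-inferiority test exists. The phrase "non-inferiority clinical trial in patients with glucose and lipid metabolism disturbances" describes the patients, not the endpoints. The Methods lead with HbA1c change, Sample Size uses HbA1c alone, and Statistical Analysis lists two-sided difference tests with no lipid margin. This stands. A reader might infer that the plan tests LDL-C and TG for non-inferiority; the documents do not support that. What remains is that the hypothesis is not limited to glucose while lipids stand among the primary outcomes and in the announced conclusion.

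Second, the Discussion nowhere says that similarity will count as lipid efficacy, and two-sided tests could show JTTZ to be better. Also true: the misreading is left open, not prescribed.

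Third, the article cites a source for LDL-C reduction with metformin and a multi-centre JTTZ trial that reported on lipids, and neither is at hand. A reader might infer that metformin has no lipid effect. The documents do not support that either; they show only that the effect is unsized for LDL-C and unaddressed for TG.

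Fourth, regression to the mean can be observed. Table 1 schedules lipids at screening and again at week 0, so the share already at target before treatment will be known, and change from week 0 avoids most of the selection effect. This stands, and the fix uses it.

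Fifth, if neither drug affects lipids, a 5% test finds no difference 95% of the time. That is the definition of the test and is not a measure of this problem.

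**Conclusion.** The concern holds as a fault in the scope of the hypothesis and in the intended conclusion, not in a stated test. On the article's own account of metformin, a similar lipid result would not support the lipid half of the Discussion's claim; an advantage over metformin would. This is so whether the Abstract or the Methods version of the primary outcome governs, because lipid target rates appear under both.

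The documents fix no numerical size. The 80% (48 per arm) and 83% (38 per arm) rest on assumed rates of 20% and 30%, and the regression-to-the-mean ranges on assumed means and SDs. The argument needs none of these values. It needs only that metformin's lipid effect is not established in the article and that no untreated or lipid-active arm is present. A reader might go further and infer that the trial can say nothing about lipids. That is too strong: superiority over metformin would remain interpretable.

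**What to change.** - **Hypothesis (Background, Study Design):** limit non-inferiority to change in HbA1c.
- **Lipids (Statistical Analysis):** keep the two-sided between-group comparison and read it as superiority. Pre-specify one measure each for LDL-C and TG, preferably the week-12 value adjusted for the week-0 value, and control multiplicity across the two, for example by Holm. Leaving open any of four tests (two lipids, rates and changes) would carry a false-positive risk of 1 − 0.95⁴ = 18.5% if they were independent; even two unadjusted tests carry 1 − 0.95² = 9.75%.
- **Target rates:** report the LDL-C and TG rates descriptively, beside the share already at target at week 0.
- **Discussion:** say that the trial compares glucose control with that of metformin, that a lipid effect will be claimed only for a measure on which JTTZ is superior after adjustment, and that a similar or non-significant lipid result will not be reported as lipid efficacy.

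Visits, drugs and patient numbers do not change. The cost is a harder lipid claim in a trial sized for HbA1c only, with no stated power for lipid superiority. As a guide, with 38 per arm and 80% power, the detectable difference without baseline adjustment is (1.960 + 0.842) × √(2/38) = 0.64 SD at the 5% level, and (2.241 + 0.842) × √(2/38) = 0.71 SD at the 2.5% level of the first Holm step. Adjustment for the week-0 value would lower both. The sponsor should state the power for a plausible lipid difference.

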### Registration

The study was registered at ClinicalTrials.gov (NCT04623567) on November 5, 2020 (https://clinicaltrials.gov/ct2/show/NCT04623567).

## Methods

### Study Design

This study is a randomised, positive drug parallel-controlled, open-label, non-inferiority clinical trial in patients with glucose and lipid metabolism disturbances. In total, 96 patients diagnosed with T2DM and dyslipidaemia will be recruited for this study. The patients will be randomly divided into two groups and treated with the JTTZ recipe or metformin for 12 weeks. This study protocol follows the Standard Protocol Items: Recommendations for Interventional Trials. (Chan et al., 2013). (Supplementary File S1). The study flow is illustrated in Figure 1. All information related to the treatment schedule is presented in Table 1.

**FIGURE 1 F1:**
[figure not shown]
Flow diagram of the study design.

**TABLE 1 T1:** Schedule of enrolment, assessments, and data collection.

Period	Enrolment/Baseline	Allocation	Treatment period			Follow-up period
Time points	Introduction period	0week	4 weeks	8 weeks	12 weeks	48weeks
Eligibility screening	×	—	—	—	—	—
Informed consent	×	—	—	—	—	—
Physical Examination	×	×	—	—	—	—
Characteristic	×		—	—	—	—
Random allocation	—	×	—	—	—	—
Interventions	—	—	×	×	×	—
Clinical Assessments	—	—	×	×	×	—
Medical history	×	×	×	×	×	×
Body weight	×	×	×	×	×	—
Waist circumference	×	×	×	×	×	—
Body mass index	×	×	×	×	×	—
Electrocardiogram	—	×	—	—	×	—
Routine urinalysis	—	×	—	—	×	—
Complete blood count analysis	—	×	—	—	×	—
HbA1c	—	×	—	—	×	×
FPG	×	×	×	×	×	×
2 h-PG	×	×	—	—	×	×
Blood lipid indicators	×	×	—	—	×	×
TCM symptom score	×	×	×	×	×	×
Liver and kidney function	—	×	×	×	×	—
Islet function	—	×	—	—	×	×
Urinary microalbumin	—	—	—	—	—	×
Urinary microalbumin/-creatinine ratio	—	—	—	—	—	×
Cardiac ultrasound	—	—	—	—	—	×
Carotid artery ultrasound	—	—	—	—	—	×
Biological specimens	—	×	—	—	×	—
Adverse event	—	×	×	×	×	—

FPG, fasting plasma glucose; PG, plasma glucose; TCM, traditional Chinese medicine.

### Patient Recruitment

This study aims to include 96 patients with T2DM and dyslipidaemia. Patients are recruited at the Guang’anmen Hospital, China Academy of Chinese Medical Sciences (Beijing, China). Recruitment advertisements are posted on webpages and notice boards in the hospital, presenting a brief description of the study aims, medicines and medical examinations involved, eligibility criteria, and the ways to participate in this study. Patients who fulfil the inclusion criteria and provide consent to participate in this study may be examined. Investigators will explain the study aims, requirements, and interventions to the prospective patients and ensure their understanding of the study parameters ahead of asking for their consent to participate. Patient eligibility will be confirmed by examinations performed at the endocrinology clinic by two endocrinology physicians, both of whom need to confirm patient suitability for this study. In addition, demographic characteristics, and reasons for non-participation of ineligible patients will be recorded. Recruitment began in October 2021 and will continue until July 2022. No patient was or will be involved in the design of this study, recruitment process, performing of study procedures, results reporting, or dissemination of the study findings. Physical examination, laboratory tests, and interventions will be free of charge. However, the study may not compensate its participants.

### Eligibility Criteria

#### Diagnostic Criteria of T2DM

The diagnostic criteria for T2DM are based on the *Guideline for the prevention and treatment of type 2 diabetes mellitus in China* (2020 edition), (China Diabetes Society, 2021), and include diabetic symptoms (increased thirst and urine volume, unexplained weight loss) plus any of the following: 1) random blood plasma glucose (blood glucose at any time of the day regardless of the time of last meal) levels ≥11.1 mmol/L (200 mg/dl); 2) fasting plasma glucose (FPG) level ≥7.0 mmol/L (126 mg/dl); 3) 2-h plasma glucose (2-h PG) level ≥11.1 mmol/L (200 mg/dl); and 4) glycated haemoglobin (HbA1c) level ≥6.5%.

In the absence of any symptom of diabetes, blood glucose measurements will be repeated on another day to confirm the diagnosis.

#### Diagnostic Criteria of Dyslipidaemia

The diagnostic criteria of dyslipidaemia are based on the *Chinese Guidelines on Prevention and Treatment of Dyslipidaemia in Adults* (2016, revision edition) (Chinese Joint Committee for Developing Chinese Guidelines on Prevention and Treatment of Dyslipidemia in Adults, 2016) and include any of the following: total cholesterol (TC) level ≥6.2 mmol/L (240 mg/dl), LDL-C level ≥4.1 mmol/L (160 mg/dl), high-density lipoprotein cholesterol level <1.0 mmol/L (40 mg/dl), and triglyceride (TG) level ≥2.3 mmol/L (200 mg/dl).

#### Diagnostic Criteria of TCM Syndrome

The diagnostic criteria for excess heat in the stomach and intestines syndrome are based on the *International Traditional Chinese Medicine Guideline for Diagnostic and Treatment Principles of Diabetes.* (Lian et al., 2020). The primary symptoms include abdominal distension, gastric stuffiness, and constipation. The secondary symptoms include dry mouth, bitter taste, or foul breath, thirsty and fondness for cold drinks, abnormally increased appetite with frequent hunger, red tongue with yellow coating, and rapid and forceful pulse.

The diagnosis of excess heat in the stomach and intestines syndrome is based on the presence of one main and two secondary symptoms. The TCM symptom scoring standard is presented in Supplementary File S2.

#### Inclusion Criteria

Patients are eligible for this study if they meet the following criteria: 1) age of 18–70 years at the time of enrolment; 2) diagnosis of T2DM plus 7.0 mmol/L (126 mg/dl) ≤ FPG level ≤13.9 mmol/L (250 mg/dl), or 2-h PG level ≥11.1 mmol/L (200 mg/dl) at the time of enrolment; 3) diagnosed with dyslipidaemia plus LDL-C level ≥3.4 mmol/L (130 mg/dl) and having TG level >1.7 mmol/L (150 mg/dl) at the time of enrolment; 4) have a body mass index ≥24.0 kg/m^2^ or waist circumference ≥90 cm for men and ≥80 cm for women; 5) failure to take anti-diabetic drugs regularly to reach normal blood glucose and lipid levels after diet control and exercise therapy before enrolment; 6) TCM syndrome differentiation as excess heat in the stomach and intestines syndrome; and 7) provision of signed informed consent form.

